**Fig. 1 Fig1:**
[figure not shown]
Flow chart of the trial

The trial was approved by the Swedish Ethical Review Authority (ID: 2023–02329-01) and was preregistered on Clinicaltrials.gov and Open Science Framework (osf.io) before data collection started. Data will be reported in accordance with The Consolidated Standards of Reporting Trials statement for nonpharmacological trials (CONSORT) and Consolidated Health Economic Evaluation Reporting Standards (CHEERS) irrespective of outcome. All study personnel will be trained in Good Clinical Practice (GCP). Quality and safety aspects of the trial will be monitored by an external part (A + Science).

## Methods

### Study setting {9}

The study will be conducted at an outpatient psychiatric clinic in Stockholm, Sweden, which is funded by public resources.

### Eligibility criteria {10}

To ensure the study’s external validity, we will adopt broad inclusive eligibility criteria. Participants presenting with comorbidities such as neuropsychiatric disorders, depression, and substance abuse will be evaluated for inclusion based on meeting all other specific inclusion/exclusion criteria. The primary diagnosis for inclusion will be PTSD.

Please see Table 1 for a comprehensive outline of the inclusion and exclusion criteria.

**Table 1 Tab1:** Inclusion and exclusion criteria

Inclusion criteria	≥ 18 years of age
	Primary diagnosis of PTSD according to DSM-5
	Signed informed consent
	Able to attend either iPE or 15 weekly sessions of PE
	Being fluent in Swedish
Exclusion criteria	Initiation or adjustment of any psychotropic medication within the last 4 weeks prior to inclusion
	Serious mental health symptoms, such as mania, psychosis, alcohol, or substance use disorders or current suicide risk warranting immediate clinical attention
	Ongoing evidence-based trauma-focused psychological treatment
	Ongoing trauma-related threat (e.g., living with a violent spouse)

### Informed consent {26a}

Informed consent will be obtained during the registration in the secure digital platform requiring two-step authentication.

### Additional consent provisions for collection and use of participant data and biological specimens {26b}

This trial does not involve collecting biological specimens for storage.

### Interventions

#### Explanation for the choice of comparators {6b}

The trial will compare prolonged exposure to weekly delivered sessions, which is considered first-line treatment [9].

### Intervention description {11a}

#### Intensive treatment (iPE)

The intensive treatment adheres to the original treatment protocol for prolonged exposure [10] with three major exceptions. First, treatment is delivered for five consecutive days followed by three 60-min individual booster sessions dispersed 1, 2, and 4 weeks afterwards. Second, treatment combines individual and group formats. Each patient will receive nine individual sessions focused on confronting the memory of the traumatic event (imaginal exposure and processing) and five group sessions with psychoeducation, breathing retraining, overall rationales, and preparing work with confronting trauma-related situations in the patient’s daily life (in vivo exposure). Starting from day 2, the group sessions shift their focus to the formulation of individually tailored designed exercises for individual implementation during these sessions. Third, there is no assigned homework between treatment days; instead, time is allocated between daily sessions for working on exposure exercises.

The treatment will be delivered for an average of 7 h of treatment each day for five consecutive days. Three individual 60-min booster sessions will be conducted, which will include imaginal exposure, follow-up on in vivo exposure exercises, a comprehensive summary of the treatment and lessons learned, as well as discussions on relapse prevention and planning for continued self-practice. These booster sessions will be dispersed 1, 2, and 4 weeks after the intensive treatment week. The total treatment period is 5 weeks, which encompasses the intensive treatment and booster sessions.

Table 2 shows a typical treatment schedule for the iPE week.

**Table 2 Tab2:** A typical treatment schedule for the iPE week

Monday	Tuesday	Wednesday	Thursday	Friday
**INTRO MEETING** 9:00 – 9:30	**IMAGINAL EXPOSURE SESSION 2** 8:30 – 9:30	**IMAGINAL EXPOSURE SESSION 4** 8:30 – 9:30	**IMAGINAL EXPOSURE SESSION 6** 8:30 – 9:30	**IMAGINAL EXPOSURE SESSION 8** 8:30 – 9:30
**GROUP SESSION 1 PSYCHOEDUCATION, OVERALL RATIONALE, PREPARATION IN VIVO** 9:30 – 11:00	Break 9:30 – 10:00	Break 9:30 – 10:00	Break 9:30 – 10:00	Break 9:30 – 10:00
	**OWN WORK** 10:00 – 11:00	**OWN WORK** 10:00 – 11:00	**OWN WORK** 10:00 – 11:00	**OWN WORK** 10:00 – 11:00
**LUNCH** 11:00 – 12:00	**LUNCH** 11:00 – 12:00	**LUNCH** 11:00 – 12:00	**LUNCH** 11:00 – 12:00	**LUNCH** 11:00 – 12:00
**WALK OUTSIDE** 12:00 – 12:30	**GROUP SESSION 2** **IN-VIVO EXPOSURE** 12:00–13:45	**GROUP SESSION 3** **IN-VIVO EXPOSURE** 12:00–13:45	**GROUP SESSION 4** **IN-VIVO EXPOSURE** 12:00–13:45	**GROUP SESSION 5** **IN-VIVO EXPOSURE** 12:00–13:45
Break 12:30 – 13:00				
**IMAGINAL EXPOSURE SESSION 1** 13:00 – 14:00				
	Break 13:45 – 14:00	Break 13:45 – 14:00	Break 13:45 – 14:00	Break 13:45 – 14:00
Break 14:00 – 14:15	**IMAGINAL EXPOSURE SESSION 3** 14:00 – 15:00	**IMAGINAL EXPOSURE SESSION 5** 14:00 – 15:00	**IMAGINAL EXPOSURE SESSION 7** 14:00 – 15:00	**IMAGINAL EXPOSURE SESSION 9** 14:00 – 15:00
**OWN WORK** 14:15 – 15:15				
	Break 15:00 – 15:15	Break 15:00 – 15:15	Break 15:00 – 15:15	Break 15:00 – 15:15
	**OWN WORK** 15:15 – 16:15	**OWN WORK** 15:15 – 16:15	**OWN WORK** 15:15 – 16:15	**OWN WORK** 15:15 – 16:15

#### Weekly prolonged exposure

Patients will receive 15 weekly 90-min sessions of individual prolonged exposure for PTSD according to the standard treatment delivery protocol. In session 1, a comprehensive overview of treatment rationale will be provided, along with the selection of the index trauma, which will be the focus of imaginal exposure and breathing retraining. Session 2 will include psychoeducation on trauma and PTSD, along with a rationale for in vivo exposure and the construction of an in vivo hierarchy. In session 3, imaginal exposure including processing for the trauma will commence following an overall rationale of this core treatment component. Starting from session 4 and continuing through session 14, participants will engage in imaginal exposure during the sessions and continue in vivo exposures outside of the therapy sessions. Assigned homework during the treatment weeks will include reading treatment material, practice breathing retraining, listen to recordings of imaginal exposure, and conducting in vivo exercises. Session 15 will include a summary of the treatment and lessons learned, as well as relapse prevention and planning of continued self-practice.

### Criteria for discontinuing or modifying allocated interventions {11b}

Participants have the right to withdraw their consent to participate in the treatment and the trial at any time point. In the event of an increase in suicidal ideation, an assessment will be conducted to determine if a referral to another appropriate resource is necessary.

### Strategies to improve adherence to interventions {11c}

The therapist will contact participants who cancel or do not show up at appointments by phone, and if the participant cannot be reached, send the participant a letter according to established clinical routines.

### Relevant concomitant care permitted or prohibited during the trial {11d}

Please see the predefined inclusion and exclusion criteria; participants must have maintained a stable dose of any psychotropic medication for a minimum of 4 weeks before entering the study. Additionally, concurrent participation in any other ongoing trauma-focused CBT or Eye Movement Desensitization and Reprocessing therapy is not permitted at the time of inclusion in the study and participants are recommended not to initiative these types of treatment throughout the treatment duration.

### Provisions for posttrial care {30}

Upon the termination of the study, participants identified as requiring additional treatment will receive assistance in locating suitable and appropriate follow-up care.

### Outcomes {12}

Table 3 presents the flow of the recruitment and treatment process and lists clinician-rated and self-rated assessments at the different time points.

**Table 3 Tab3:** The flow of the recruitment and treatment process

	Enrollment	Allocation	Baseline	Week 1–5	Week 6–15	Posttreatment	1-month follow-up (primary end-point)	6-month follow-up	12-month follow-up
**Enrollment**									
Eligibility screen	X								
Informed consent	X								
Allocation		X							
Treatment									
Weekly PE				X	X				
iPE				X					
**Clinical administered instruments**									
CAPS-5	X						X	X	X
MINI	X								
**Self-rated instruments**									
PCL-5^a^			X	X	X	X	X	X	X
ITQ^a^			X	X	X	X	X	X	X
PHQ-9^b^			X		X	X	X	X	X
EQ-5D^b^			X		X	X	X	X	X
AQoL-6D^b^			X		X	X	X	X	X
TIC-P^b^			X		X	X	X	X	X
NEQ^b^					X	X	X	X	X
CEQ^c^				X					
WAI-SR^d^				X					
Treatment preference	X						X		
SUD-ratings^e^				X	X				

*Abbreviations*: *AQoL-6D* Assessing Quality of Life 6 Dimensions, *CAPS-5* Clinician-Administered PTSD Scale for DSM-5, *CEQ* Credibility/Expectancy Questionnaire, *ITQ* The International Trauma Questionnaire, *MINI* Mini International Neuropsychiatric Interview, *NEQ* Negative Effects Questionnaire, *SUD* Subjective Units of Distress Scale, *TIC-P* Treatment Inventory of Costs in Psychiatric Patients, *PHQ-9* Patient Health Questionnaire, *WAI-SR* Working Alliance Inventory–Short Form Revised

^a^PCL-5 and ITQ are administered daily during the intensive phase of treatment in the I-PE group

^b^PHQ-9, EQ-5D, AqoL-6D, TIC-P, and NEQ are administered immediately after treatment completion, w5 in the I-PE arm and w15 in the weekly delivered PE arm

^c^CEQ is administered after the first individual session in each treatment format

^d^WAI-SR is administered at the third individual session in each treatment format

^e^SUD-ratings are collected each individual treatment session

The primary outcome measure is the gold-standard clinical interview CAPS-5 that assesses PTSD symptom severity and past month diagnosis of PTSD [11] administered at enrollment, 1 month after treatment completion (primary endpoint), and at 6- and 12-month follow-ups. The CAPS-5 total severity score has high internal consistency (Cronbach’s *α* = 0.88) and interrater reliability (intraclass correlation coefficient = 0.91) and good test–retest reliability (intraclass correlation coefficient = 0.78) [11]. In this study, treatment response will be deemed successful if there is a minimum improvement of 10 points on the CAPS-5 scale between baseline and the participant’s last recorded measurement within the baseline to 12-month follow-up period. Remission will be defined as the absence of a PTSD diagnosis and/or a CAPS-5 total symptom severity score below 24, following the criteria set by Blevins et al. [12]. To be categorized as having achieved recovery, participants must maintain their remission status through the subsequent follow-up assessment.

Secondary self-rated outcome measures are the Post-traumatic Stress Disorder Checklist for DSM-5 (PCL-5; [12]) and the International Trauma Questionnaire (ITQ; [13, 14]). These instruments are utilized to capture self-rated symptoms of PTSD and complex PTSD. Treatment response on the PCL-5 will be defined as a reduction of 10 points or more from the baseline score. Remission will be determined by a score below 30 on the PCL-5, as identified in the Swedish version of the scale by Bondjers [15], which is indicative of probable PTSD. To be classified as having achieved recovery, participants must maintain their remission status through the subsequent follow-up assessment.

Additionally, the level of depressive symptoms will be assessed using the Patient Health Questionnaire (PHQ-9; [16, 17]), and quality of life will be assessed using the EQ-5D [18].

The Assessing Quality of Life 6 Dimensions (AQoL-6D; [19]) will be administered to calculate quality-adjusted life-years for cost-utility analysis. The Treatment Inventory of Costs in Psychiatric Patients will be used to collect information on the use of medical resources, medication, social care, absenteeism, and presenteeism (TIC-P; [20]).

The Negative Effects Questionnaire (NEQ; [21]) will be used to capture potential adverse events immediately after treatment completion and the upcoming assessment points. An open-ended question asking for the occurrence of any adverse events will also be administered at each treatment session.

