### Sample size {14}

A power calculation was conducted to determine the number of participants needed to evaluate intensive treatment compared to weekly delivered sessions. The power analysis for the trial is based on the CAPS-5, where a significant difference in treatment effects between groups would be set to at least 10 points. With an estimated standard deviation of the CAPS-5 of 20, this represents a standardized mean difference in terms of Cohen’s *d* of 0.5 [24]. Given 95% power, 10% data attrition rate, and an alpha level of 0.05, we estimate that we would need a total of 140 participants to find a statistically significant moderate between-group effect of *d* = 0.5 at our primary endpoint (1 month). We also conducted a power analysis to ensure that we would be able to detect our expected differences in dropout rate, a reduction in the dropout rate from a 22% baseline rate to 5% in the intervention group with conditional linear regression, conditional on the four randomization strata arising from the combination of sex (male, female) and trauma onset (childhood, adulthood). The power was estimated with 1000 randomly generated datasets. The following table shows the estimated power with different sample sizes (*n*).

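### CAPS-5 response is read at each participant's latest score up to 12 months, which mixes time points and can tilt the secondary response comparison toward iPE if treatment dropouts also miss CAPS-5 visits

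*Protocol article*

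**What the plan says.** All of this is in the protocol article.

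- **Response.** Outcomes {12}, in the text under Table 3, states that "treatment response will be deemed successful if there is a minimum improvement of 10 points on the CAPS-5 scale", counted from baseline to the participant's "last recorded measurement within the baseline to 12-month follow-up period".
- **Schedule.** The same paragraph has CAPS-5 "administered at enrollment, 1 month after treatment completion (primary endpoint), and at 6- and 12-month follow-ups". Table 3 shows none during treatment or immediately after it.
- **Use.** Objectives {7} lists response and remission rates among the additional between-arm comparisons. The primary comparison is clinician-rated severity at 1 month, with further comparisons at 6 and 12 months.
- **Dropout.** Sample size {14} plans for "a reduction in the dropout rate from a 22% baseline rate to 5% in the intervention group". For the primary outcome it assumes a single loss figure, not split by arm: "Given 95% power, 10% data attrition rate, and an alpha level of 0.05".
- **Retention.** Treatment variables asks those who leave treatment to stay in the outcome assessments. Section {18b} adds reminders, phone calls and letters.
- **Remission.** Outcomes {12}: "Remission will be defined as the absence of a PTSD diagnosis and/or a CAPS-5 total symptom severity score below 24". Recovery is then defined as remission that holds at the next follow-up.

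**The concern.** The response rule fixes no visit. One participant is classified at 12 months, another at 6 and another at 1, according to when they were last seen. The resulting rate belongs to no stated time point, although the objectives are framed at 1, 6 and 12 months. Trial status has analysis starting in October 2025, while follow-up runs to October 2026. If response is reported at that first analysis, early recruits could be read at 12 months and late recruits at 1 month, and a participant's status could change in a later report.

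The window also includes baseline. A participant lost before the 1-month visit has only the enrolment CAPS-5, hence zero change, and counts as a non-responder on a literal reading. If such losses are more common in weekly PE, as the planned dropout rates suggest they might be, the response comparison moves toward iPE with no difference in the effect of treatment. What is at stake is a secondary comparison that readers will find easy to quote.

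**Working it through.** **Reproducing the protocol's own figure.** The 22% vs 5% inputs come from the dropout power table in Sample size {14}, which gives 0.878 at N = 140. Simulated conditional logistic regression (likelihood-ratio test, four near-equal strata, two-sided 0.05, 2,000 datasets) gives 0.8785. At N = 100, 120 and 160 it gives 0.750, 0.832 and 0.912, against the stated 0.759, 0.820 and 0.925. The section names a linear regression; a linear model with strata gives 0.857 at N = 140. The dropout inputs are therefore read as intended.

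**Inputs for the response check**

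- Dropout 22% (weekly PE) and 5% (iPE): Sample size {14}.
- Overall attrition 10%: same section.
- 70 per arm: N = 140, 1:1.
- True response r = 60% in both arms: the Background's approximate figure, used as an illustration, with an assumed range of 50% to 70%.
- Share s of dropouts with no CAPS-5 after baseline: not given, so varied from 0 to 1.

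**Formula.** If those with no later CAPS-5 count as non-responders, observed response = r × (1 − s × dropout). With equal true response the spurious difference is r × s × (0.22 − 0.05).

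**No dropout assessed (s = 1)**

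| True response | Weekly PE | iPE | Spurious difference | Rejection rate, nominal 5% test |
|---|---|---|---|---|
| 50% | 0.78 × 0.50 = 39.0% | 0.95 × 0.50 = 47.5% | 8.5 points | about 17% |
| 60% | 0.78 × 0.60 = 46.8% | 0.95 × 0.60 = 57.0% | 10.2 points | about 23% |
| 70% | 0.78 × 0.70 = 54.6% | 0.95 × 0.70 = 66.5% | 11.9 points | about 30% |

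The rejection rates come from simulating a pooled two-proportion z test with 70 per arm.

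**Some dropouts assessed (r = 60%)**

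- s = 0.5: 0.60 × 0.5 × 0.17 = 5.1 points.
- s = 0.25: 2.6 points.
- s = 0: 0 points.

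**Starting from the planned 10% attrition (r = 60%)**

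- Equal by arm: 54.0% in both, 0 points.
- Split 22:5: 20% × 22/27 = 16.3% and 20% × 5/27 = 3.7%. Observed response is 50.2% vs 57.8%, a difference of 7.6 points, with rejection about 15%.

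**If dropouts truly respond less.** With s = 1 and completers at 60%, the observed gap stays at 10.2 points. Suppose dropouts respond at 30% (an assumption). True response is then 0.78 × 0.60 + 0.22 × 0.30 = 53.4% and 0.95 × 0.60 + 0.05 × 0.30 = 58.5%. That is a real gap of 5.1 points, so only 10.2 − 5.1 = 5.1 points is spurious.

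**Loss only after the 1-month visit.** Suppose 22% vs 5% are read at 1 month and the rest at 12 months, and response drifts from 60% to 70%. Weekly PE shows 0.22 × 0.60 + 0.78 × 0.70 = 67.8%; iPE shows 0.05 × 0.60 + 0.95 × 0.70 = 69.5%. The difference is +1.7 points, or −1.7 if response drifts to 50%. Nearly all of the possible bias therefore comes from participants who have only a baseline score.

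**The case against.** The best defence is that dropout is not missing data. The protocol defines completion by treatment sessions and keeps those who leave treatment in the assessment schedule, with active contact when visits are missed. Its own figures point the same way: losing every dropout would mean (22% + 5%)/2 = 13.5% missing, more than the 10% planned. A reader might infer that the dropout gap by itself must produce a response advantage of about 10 points, or that an iPE advantage would come wholly from dropout. The documents do not support that. The 10.2 points is the upper case at 60% response, and the range starts at 0.

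The Background also attributes the roughly 60% response partly to dropout, so 60% is not a dropout-free rate, and those who leave may truly respond less. Counting them as non-responders is then partly correct. Better completion is moreover a benefit that the trial hopes to show.

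Finally, the protocol does not say outright how a participant with no later CAPS-5 is classified, and the analysis plan on OSF, which is not shown here, may address it.

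These arguments limit the size and leave the rule standing. The protocol itself sets the time point, and its window includes baseline. The statement in section {20c} that models use all available data does not change a classification made from each person's latest score. The lack of a 1-month response rate holds whatever the attrition.

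**Conclusion.** The definition should be changed. It mixes visits, yields no response rate at the primary endpoint, and can bias the secondary between-arm response comparison toward iPE. At an equal true response of 60% the bias runs from 0 to 10.2 points, and is 7.6 points if the planned attrition splits 22:5. The upper end assumes that no dropout attends a CAPS-5 visit, that a missing later score counts as non-response, and that dropouts would have responded like everyone else. The primary comparison of CAPS-5 severity at 1 month does not use this rule and is not affected.

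The remission wording is a separate and smaller point. 'And/or' leaves open whether either criterion suffices or both are needed, and recovery inherits the ambiguity. A reader might infer that both must be required. The documents do not show which rule is right: they defer to a cited source that is not at hand, and the same reference number is given for the self-rated PCL-5.

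**What to change.** Define CAPS-5 response (at least 10 points from baseline) separately at the 1-, 6- and 12-month visits, with 1 month leading. Handle missing CAPS-5 by multiple imputation or a mixed model, not by the last record, and bring the analysis plan into line. The PCL-5 scores collected during treatment (Table 3) could inform the imputation. If the missingness is adequately modelled, equal true response then gives an expected difference of 0 and a rejection rate of about 5%.

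The cost is a change to the definition and no new data. The downside is reliance on a missing-at-random type of assumption. A sensitivity analysis that counts missing as non-response can check it and shows how much of any difference depends on loss to assessment. Reporting CAPS-5 availability by arm and visit would show where the trial falls in the 0 to 10.2 range.

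For remission, state one rule before unblinding and report both components, diagnosis and score below 24, alongside it.

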## Objectives {7}

The main objectives are to investigate the efficacy of intensive exposure-based treatment (iPE) for PTSD in a randomized controlled trial (*N* = 140) comparing iPE with weekly delivered prolonged exposure. The trial will encompass an assessment of health-economic factors from two distinct viewpoints: one from the standpoint of the treatment provider (comprising direct expenses such as healthcare personnel costs) and the other from a more extensive societal standpoint (encompassing indirect expenses such as sick leave). Additionally, we will measure treatment-related transformational processes and factors that can influence treatment results.

The two types of treatment formats will be compared 1 month after treatment completion in each respective treatment arm (primary endpoint) and at the 6-month and 12-month follow-ups regarding clinician-rated PTSD symptom severity by assessors masked to treatment allocation. In addition, comparisons in relation to self-rated symptoms of PTSD and complex PTSD, depression and quality of life, recovery rate, response and remission rates, number of dropouts, cost-effectiveness, adverse events, treatment mediators and moderators, credibility, satisfaction with treatment, and perceived alliance with the therapist will be made. Due to its shorter format, we expect the intensive treatment format to provide a faster response than first-line treatment.

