#### Methods in analysis to handle protocol nonadherence and any statistical methods to handle missing data {20c}

All available data will be used in the models. Screening, recruitment, consent forms, withdrawal, amendments to protocol and occurrence of protocol deviations, and serious adverse events will be monitored by A + Science. In case of detected irregularities, additional on-site monitor visits will be scheduled.

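### CAPS-5 response is scored at each participant's last recorded assessment, so the response-rate comparison has no fixed time point and can be biased if CAPS-5 loss differs by arm

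*Protocol article*

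**What the plan says.** Outcomes {12}, in the text after Table 3, defines CAPS-5 response by the size of a change and by where that change ends. On size, "treatment response will be deemed successful if there is a minimum improvement of 10 points on the CAPS-5 scale between baseline". The value at which the change ends is, for each person, the "last recorded measurement within the baseline to 12-month follow-up period". The same paragraph says that CAPS-5 is "administered at enrollment, 1 month after treatment completion (primary endpoint), and at 6- and 12-month follow-ups". Table 3 agrees: there is no CAPS-5 during treatment or at its end.

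Objectives {7} compares clinician-rated severity at 1, 6 and 12 months. Its next sentence lists further between-arm comparisons, among them "recovery rate, response and remission rates, number of dropouts", and attaches no visit to them.

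Four other statements bear on the size of the problem:

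- Sample size {14} powers the dropout comparison for "a reduction in the dropout rate from a 22% baseline rate to 5% in the intervention group". Separately, it allows 10% data attrition for the primary endpoint, not split by arm.
- Treatment variables, under Outcomes {12}, says that participants who leave treatment are encouraged to attend all outcome assessments.
- Background {6a} puts response to treatments such as PE at around 60%, and attributes the shortfall partly to dropout.
- Trial status has analysis starting once primary-endpoint data are complete (October 2025), with the last follow-up in October 2026.

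**The concern.** The rule carries the last observation forward, over a window that opens at baseline. Two things follow from the wording alone.

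First, the visit that is scored depends on how long each person was followed. A participant who responds at 1 month and has relapsed by 12 months is a non-responder if fully followed, but a responder if lost after 1 month. Completeness of follow-up thus changes the outcome itself, and a single response rate pools results from up to three different times after treatment.

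Second, a participant with no CAPS-5 after enrolment has the baseline value as the last record. The change is then zero and the person is a non-responder by construction.

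What is at stake is the between-arm comparison of response rates. It has no stated time, it cannot be set beside the 1-month primary result, and it can favour the arm with better CAPS-5 retention.

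**Working it through.** **The plan's own figure.** The article gives no power or expected rate for the response comparison. The nearest figure is the power of 0.878 at n = 140 to detect dropout of 22% against 5%. A simulation of a linear regression of dropout on arm and four equal strata (two-sided 0.05, 4,000 datasets) gave 0.863, so the dropout rates are being read as the plan uses them.

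**Inputs.** 70 per arm (140 randomised 1:1). True response 60% in both arms, an illustrative value taken from Background {6a}. Two-sided alpha of 0.05, since the article does not state sidedness. The share of each arm never reassessed on CAPS-5 is not in the article and is an assumption throughout.

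**Formula.** Let *L* be the share of an arm with no CAPS-5 after enrolment, and *q* the true response rate among those lost, taken as the same in both arms. The rule scores all of them as non-responders, so each arm's rate falls by *Lq* and

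spurious difference (iPE − weekly) = *q* × (*L*weekly − *L*iPE).

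**Splitting the 10% attrition 22:5 (assumed).** The two arms must average 10%, so the scale factor is 0.20/0.27 = 0.741. This gives *L*weekly = 0.22 × 0.741 = 0.163 and *L*iPE = 0.05 × 0.741 = 0.037.

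- Weekly: 0.60 × (1 − 0.163) = 50.2%
- iPE: 0.60 × (1 − 0.037) = 57.8%
- Difference: 7.6 points
- Standard error: √(2 × 0.54 × 0.46/70) = 0.084, so the shift is 0.076/0.084 = 0.90 and P(|Z + 0.90| > 1.96) = 0.147. The exact binomial calculation gives 14.8%.

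**Range.** Rejection rates below are exact, for the pooled two-proportion test with 70 per arm and 60% true response in everyone, including those lost.

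| Assumed CAPS-5 loss (weekly / iPE) | Spurious difference | Rejection rate |
|---|---|---|
| None | 0 | 4.9% |
| 10% / 10% | 0 | 5.1% |
| A quarter of the 22% / 5% dropouts | 2.6 points | 6.0% |
| Half of them | 5.1 points | 9.3% |
| 16.3% / 3.7% | 7.6 points | 14.8% |
| All of them (22% / 5%) | 0.60 × 0.17 = 10.2 points | 23.0% |

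In the last row, true response of 50% or 70% gives 8.5 points (17.3%) or 11.9 points (29.8%).

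If those lost would respond at 30% rather than 60%, the bias is 0.30 × 0.126 = 3.8 points with the 16.3/3.7 split, and 0.30 × 0.17 = 5.1 points with 22/5. If none of them would respond, it is nil.

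**Visit mix at an early data cut.** This applies only if response is reported when the 1-month data are complete. Counting 4, 26 and 52 weeks from the end of treatment (week 5 or week 15), the visits fall at weeks 9, 31 and 57 for iPE and 19, 41 and 67 for weekly PE. Assume uniform entry over 104 weeks, no start delay, no loss, and a cut at 104 + 19 = week 123.

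- iPE: 12-month value (123 − 57)/104 = 63%; 12- or 6-month value (123 − 31)/104 = 88%. The split over 12, 6 and 1 months is 63/25/12%.
- Weekly: (123 − 67)/104 = 54%; (123 − 41)/104 = 79%. The split is 54/25/21%.

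The gap in the 12-month share is 10/104 = 9.6 points. It does not depend on the exact cut: at week 108, about October 2025, the shares are 51/104 = 49.0% and 41/104 = 39.4%.

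**The case against.** A reader might infer that the rule is bound to bias the comparison because the plan expects dropout of 22% against 5%. The article does not support that. Those figures are treatment dropout. Participants who leave treatment are to be encouraged to attend every assessment, and section {18b} adds reminders, calls and letters. The only stated data loss is 10%, with no split by arm, and it refers to the 1-month endpoint: a person who misses that visit but attends later has a real value under the rule. The 60% also already reflects dropout in part, so applying it to everyone, including those lost, leans towards a larger bias. All of this stands, and it makes the bias conditional.

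A reader might also see a contradiction with "All available data will be used in the models" in section {20c}. That sentence concerns models, and a responder classification does not contradict it. Nor is it an error that "Treatment response on the PCL-5 will be defined as a reduction of 10 points or more from the baseline score" names no visit, since a visit may be fixed in the separate analysis plan. The statement that "we expect the intensive treatment format to provide a faster response than first-line treatment" fits the research question on speed of recovery better than a response proportion, so it does not settle when response should be scored.

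The data-cut argument is conditional too. Trial status does not say that response is analysed at the first cut, and the arm difference in visit mix at that cut would not arise if response were computed only after all 12-month visits.

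Finally, response is not the primary outcome, is not among the secondary outcomes named in the abstract, and is not one of the listed research questions. That limits the weight of the point. None of these objections removes the mixing of visits, which follows from the stated rule as soon as some participants miss a later visit.

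**Conclusion.** The point holds as a defect in a stated definition. CAPS-5 response has no fixed visit, the scored visit depends on completeness of follow-up, and the literal wording makes non-responders of people never reassessed. These conclusions rest only on the wording of Outcomes {12}.

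The bias in the arm comparison is possible, not established. At 60% true response it runs from 0 to about 10 points. It is nil if loss and response among those lost are equal between arms, or if those lost would not have responded. Where greater loss in the weekly arm produces it, it favours iPE, the arm the trial hopes to show superior. The 7.6-point and 10.2-point cases rest on assumed loss patterns that the article does not state.

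The continuous CAPS-5 comparison at 1 month and the sample size are untouched. The definition should be changed, but the trial's main conclusion does not depend on it.

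**What to change.** In Outcomes {12}, define CAPS-5 response as an improvement of at least 10 points from the enrolment CAPS-5 at the 1-month visit, and separately at 6 and at 12 months. State that missing visits are handled under the same missing-data assumption as the continuous CAPS-5 analysis. Keep last-observation scoring, or scoring missing as non-response, as a sensitivity analysis only.

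With response at one visit and missing values handled under an assumption that holds, equal true response of 60% gives an expected difference of zero and a rejection rate of 4.9% with 70 per arm.

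The cost is one sentence in the outcome definitions and a matching line in the analysis plan. No new data are needed, because CAPS-5 is already scheduled at all three visits.
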